## 5. Statistical Analysis

Descriptive and inferential statistical analysis will be carried out. The normality of the variables under consideration will be tested with the Shapiro–Wilk test. Possible dependencies between qualitative variables and categorical scales characteristics of the three different groups will be investigated using Pearson’s chi-squared test (χ^2^).

A paired t-test or the non-parametric Wilcoxon signed-rank test was performed to analyze whether there was any significant improvement in the cognitive function and mood (ACE-R, MMSE, TMT A-B, DST F-B, and GDS-15) and functionality (SFT, BBS, IADL, and IPAQ) after the subjects had completed the 12 weeks intervention of the two different exercise programs.

In order to investigate differences between groups, at baseline and after the intervention, one-way ANOVA F-tests, or Kruskal–Wallis tests for more than two independent samples will be carried out for all the mentioned variables, both at baseline and after the intervention (12 weeks). Bonferroni correction was applied to adjust for multiple pair-wise comparisons of the means for the main effects.

Pearson’s or Spearman’s correlation tests for the total changes from baseline will be applied accordingly to normality test. Variables correlated significantly will be used for further multivariate analysis. To further analyze the relationship between the changes of outcome measures, a multivariate linear regression analysis will also be applied for the total changes from baseline, in order to clarify the effect of exercise in cognitive function and functional performance. If group differences are observed at baseline, those variables are included as covariates in further analyses. To assess the effect on the primary and secondary outcome measures, analysis of covariance (ANCOVA) is used with cognitive domain scores on the post-tests as dependent variables, pre-test scores as covariates, and group (combined aerobic and resistance exercise program, single resistance exercise program, control) as the between-subject factor.

Statistical analyses will be carried out using the statistical software package SPSS 24.0 for Windows (SPSS Inc., Chicago, IL, USA). *p*-values less than 0.05 are considered statistically significant.

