### 2.2. Participants and Eligibility

The sample of the study population will be selected by the method of purposive sampling, observing the rules of appropriateness and adequacy.

In order to estimate the sample of patients required for any statistical relation to be established as significant, we perform a priori power analysis using the software GPower 3.1. The parameters applied included: (a) alpha level of 0.05 (b) statistical power at least of >80%, (c) the effect size or else the magnitude of the effect of the exercise is expected to be small to moderate and was determined (f = 0.23–0.24). The effect size (ES) is estimated based on previous studies on the cognitive effects of combined aerobic and strength training and single aerobic training using a similar intervention [12,13,14]. Since we are going to study multiple outcomes (cognitive function and functionality), we used the weakest exercise outcome association for sample size calculation. With the above parameters and the fact that the present study provides information for three groups, the calculator showed us that by using 171–186 participants in total, or 57–62 individuals per group, we could secure a meaningful statistical power 80% for all the assessments performed.

Participants will be recruited with the assistance of the Amarousion Day Center of the Alzheimer Society of Athens as well as from the outpatient clinic of the Athens General Hospital “G. Gennimatas”. Potential study participants are to be notified by the center’s physician. The participants will be persons with mild Alzheimer’s disease which was determined in accordance with the diagnosis (DSM-IV and NINCDS/ADRDA diagnostic criteria) [15,16].

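### The regression of changes on significance-screened changes is said to clarify the exercise effect, but it estimates an association and its p-values have no valid error rate

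*Protocol article*

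**What the plan says.** Section 5 (Statistical Analysis) sets out a two-step procedure.

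- **Screen:** "Pearson’s or Spearman’s correlation tests for the total changes from baseline will be applied accordingly to normality test". The selection rule follows: "Variables correlated significantly will be used for further multivariate analysis".
- **Regression:** a multivariate linear regression is fitted to the total changes from baseline. Its declared subject is how the changes in the outcome measures relate to each other, and its declared purpose is "in order to clarify the effect of exercise in cognitive function and functional performance".

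The sentence names no group term. The general threshold is that p-"values less than 0.05 are considered statistically significant". Bonferroni is mentioned only for pairwise comparisons of means, so no adjustment is stated for the screen or the regression.

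The same paragraph also specifies an ANCOVA for the effect on the primary and secondary outcomes, with group as factor and the pre-test score as covariate. Its dependent variables are given only as post-test scores on cognitive domains.

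**The concern.** The purpose clause asks the regression for something it cannot give. Exercise enters this trial through the randomised group. A model with changes on both sides and no group term has no coefficient for exercise, so its coefficients say how two outcomes move together, for whatever reason.

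The screen adds a second problem. Predictors are chosen because they correlate significantly with the outcome change, and are then tested on the same participants as if they had been chosen beforehand. The nominal 5% no longer describes the error rate of those tests.

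At stake is a report that cites significant change-on-change coefficients as evidence that exercise improves cognition or functional performance. Functionality is part of the primary objective in Section 3, and the ANCOVA sentence does not name functional scores, so this reading is most likely for the functional outcomes.

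**Working it through.** **Inputs from the protocol article.** Section 2.2 gives "alpha level of 0.05", "statistical power at least of >80"%, an effect size "expected to be small to moderate and was determined (f = 0.23–0.24") and "171–186 participants in total, or 57–62 individuals per group". Section 3 lists the cognitive tests, which I count as six (ACE-R, MMSE, TMT-A, TMT-B, digit span forward, digit span backward). Sections 3 and 3.1.2 give the functional measures, which I count as eight (six Senior Fitness tests, BBS, IADL). The article gives no correlations between changes, so every correlation below is an assumption shown over a range.

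**1. The plan's own figure.** For a three-group ANOVA F test with noncentrality N·f² and degrees of freedom 2 and N−3, f = 0.23 gives N = 186 (power 0.802) and f = 0.24 gives N = 171 (power 0.802). The stated range reproduces exactly and this point does not affect it.

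**2. How easily the screen is passed.** The smallest significant correlation is t/√(N−2+t²).
- N = 171: 1.974/√(169+3.897) = 0.150.
- N = 186: 1.973/√(184+3.893) = 0.144.

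By the Fisher z approximation, a true correlation of 0.2 between two changes, with no contribution from exercise, passes with probability 0.75–0.78. A correlation of 0.3 passes with probability 0.98–0.99.

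**3. Screening and testing on the same data, cognitive and functional changes unrelated.** There are 6×8 = 48 cross-domain pairs, so 48×0.05 = 2.4 pass by chance on average. With independent tests, the chance that at least one passes is 1−0.95⁴⁸ = 0.91 over all pairs and 1−0.95⁸ = 0.34 for one cognitive outcome. The table simulates the full procedure (screen at p < 0.05, then least squares on the selected changes, n = 180). Repeat runs differed by no more than about 4 percentage points.

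| Assumed within-domain correlation | At least one significant coefficient, all 48 pairs | One cognitive outcome against 8 functional |
|---|---|---|
| 0 | 91% | 33% |
| 0.3 | 84% | 28% |
| 0.5 | 65% | 18% |

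With fully independent changes, 95–96% of the variables that pass the screen are significant again in the regression, so the second step is barely a test.

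**4. Significant without an exercise effect, absent with one.** Suppose exercise does nothing but all changes share a common correlation. For one cognitive outcome against eight functional changes (N = 171 and 186), at least one coefficient is significant in 80–82% of trials at correlation 0.1 and in 93–94% at 0.3. These are genuine associations and become errors only if read as exercise effects. Conversely, if exercise raises cognition alone by 0.5 SD and the changes are otherwise independent, the correlation between a cognitive and a functional change is significant in only 5.7% of trials.

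**5. If a group term were added.** Under no exercise effect on anything, the group test stays near 5%. If exercise also moves the adjusting outcome, then with unit within-arm SDs the adjusted group coefficient is (cognitive effect) − (correlation)×(functional effect). Take an assumed correlation of 0.3 and a functional effect of 0.5 SD:
- a true 0.50 becomes 0.50 − 0.3×0.5 = 0.35;
- a true zero becomes 0 − 0.3×0.5 = −0.15.

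With 60 per arm, the second case is rejected about 13% of the time: the SE is √(1−0.09)·√(2/60)·√1.0625 ≈ 0.180, so the mean z is about −0.15/0.180 = −0.83.

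A 0.5 SD effect fits the planning value. With one arm differing from two equal arms, f = 0.23–0.24 corresponds to 3f/√2 = 0.49–0.51 SD.

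**The case against.** The strongest reply is that this is an association analysis and the plan handles the exercise effect elsewhere. The regression sentence does open by naming relationships between changes as its subject. The ANCOVA with group and baseline score keeps its 5% error, and one-way ANOVA or Kruskal–Wallis tests compare the groups on all listed variables at 12 weeks. All of that stands. A reader might infer that the trial has no sound analysis of the exercise effect; the document does not support that.

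Other stronger readings also fail.

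- **That false positives are bound to occur.** The rate depends on correlations the article does not give, and for a single cognitive outcome with unrelated functional changes it is at most about one in three.
- **That all 14 scores give 14×13/2 = 91 pairs and so 91×0.05 ≈ 4.6 false positives.** This needs every pair to be null, including pairs within one domain, where correlation is to be expected. Only the count of 2.4 among 48 cross-domain pairs is coherent.
- **That the regression would reverse a true effect.** The calculations show a true effect shrinking and a zero moving off zero, not a reversal. They also need a group term that Section 5 does not name.

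The article does not list the model's variables, and a condensed article may leave that to the full plan. My count of scores is one reading: Section 3.1.1 also sums the digit-span parts into one total, and GDS-15 and IPAQ are left out. This affects the size but not the objection, which is to the written selection rule and the written purpose. The clause on clarifying the exercise effect sits in the same sentence as the association aim, and nothing labels the analysis exploratory.

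**Conclusion.** The point holds as a flaw in a supplementary analysis and in the purpose assigned to it. The regression estimates associations between post-randomisation changes, and its p-values after the screen have no valid error rate. It can show significant coefficients when exercise does nothing: about 65–91% of trials across 48 unrelated pairs and 18–33% for one cognitive outcome, at n = 180 with within-domain correlation assumed between 0 and 0.5. It can also miss a real effect. Adding group would not repair the estimate where exercise also affects the adjusting outcome, as the assumed case shows (0.50 to about 0.35, zero to about −0.15). The sample size and the validity of the ANCOVA are untouched. The article should be corrected because it writes both the rule and the claim into the plan.

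**What to change.** In Section 5:

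1. Delete the significance screen and the phrase that gives the regression the purpose of clarifying the exercise effect.
2. State that conclusions on the exercise effect rest on the ANCOVA with randomised group and baseline score, and that its dependent variables include the functional outcomes as well as the cognitive scores.
3. If the link between cognitive and functional change is of interest, report all cognitive-by-functional associations of change, adjusted for group, with confidence intervals and no selection, labelled exploratory.

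This costs a few reworded sentences and no extra participants or data. The downside is that one set of significant-looking results is no longer available.

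### The ANCOVA is introduced for all primary and secondary outcomes but names only cognitive scores as dependent variables, and its extra covariates depend on observed baseline differences

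*Protocol article*

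**What the plan says.** Section 3 of the protocol article (Outcome Measures and Measurement Procedures) makes cognition and functionality jointly primary. SFT, BBS and IADL are the functional instruments; mood, physical activity and compliance are secondary.

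Section 5 (Statistical Analysis) then sets out several analyses:

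- Within-group paired t-tests or Wilcoxon tests, for cognition, mood, function and physical activity.
- Between-group one-way ANOVA or Kruskal–Wallis tests, which "will be carried out for all the mentioned variables, both at baseline and after the intervention (12 weeks").
- A regression on changes from baseline, said to clarify what exercise does to cognition and functional performance. Its variables are screened by correlation: "Variables correlated significantly will be used for further multivariate analysis".
- A covariate rule: "If group differences are observed at baseline, those variables are included as covariates in further analyses".
- An ANCOVA, whose stated purpose is to assess the primary and secondary outcomes: "analysis of covariance (ANCOVA) is used with cognitive domain scores on the post-tests as dependent variables, pre-test scores as covariates". Group is the between-subject factor.

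**The concern.** The last sentence has a broad purpose and a narrow list of dependent variables. SFT, BBS, IADL and GDS-15 fall within the first and outside the second. For these outcomes the section writes out no baseline-adjusted group comparison, and the 12-week group test that expressly covers them leaves out a baseline the trial collects anyway. Half of the primary objective may therefore be analysed with less precision than the data allow, and chance baseline imbalance may pass into the functional estimates. IADL shows the point. Its maximum is 8 for women and 5 for men (Section 3.1.2), so an unadjusted comparison carries any chance difference in sex mix into the group effect.

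Two further features add to this. The covariate rule lets chance imbalance, rather than prognostic value, decide which extra variables enter the model. And each cognitive outcome receives two between-group tests at 12 weeks, with no statement of which one decides.

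**Working it through.** **Inputs from Section 2.2.** Significance: "alpha level of 0.05". Power: "statistical power at least of >80"%. Effect size: it "is expected to be small to moderate and was determined (f = 0.23–0.24"). Size: "by using 171–186 participants in total, or 57–62 individuals per group". There are three groups. The pre/post correlation ρ is not in the document; it is an assumption, varied below.

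**1. The plan's own figure.** Omnibus F test with λ = N·f², df₁ = 2 and df₂ = N − 3.

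- f = 0.23, N = 186: λ = 186 × 0.0529 = 9.84, power 80.2%.
- f = 0.24, N = 171: λ = 171 × 0.0576 = 9.85, power 80.2%.

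Both ends of the stated range reproduce. Taking one further degree of freedom for a covariate, with no variance reduction, gives the same 186 and 171. The sample size therefore does not reveal whether f was meant for raw or for baseline-adjusted scores, so both cases follow.

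**2. If f is on the raw post-score scale.** Adjustment multiplies the residual variance by 1 − ρ², so λ = N·f²/(1 − ρ²) and df₂ = N − 4. At N = 186 and f = 0.23:

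| ρ | 1 − ρ² | λ | ANCOVA power | N for 80% power (f = 0.24 to 0.23) |
|---|---|---|---|---|
| 0.3 | 0.91 | 10.81 | 84.0% | 156–171 |
| 0.5 | 0.75 | 13.12 | 90.6% | 129–141 |
| 0.7 | 0.51 | 19.29 | 98.0% | 90–96 |

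**3. If f is on the baseline-adjusted scale.** The unadjusted test then has λ = N·f²·(1 − ρ²). At N = 186 and f = 0.23:

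- ρ = 0.5: λ = 7.38, power 67.2%.
- ρ = 0.7: λ = 5.02, power 49.8%.

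**4. Two tests on one outcome.** Null simulation with three groups of 60 and 20,000 runs per ρ. Each test alone rejects in 4.9–5.2% of runs. Rejecting if either ANOVA or ANCOVA gives p < 0.05:

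- ρ = 0.5: 7.5%.
- ρ = 0.7: 8.3%.
- ρ = 0.8: 8.7%.

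**5. Unadjusted test when the baseline happens to differ.** Same simulation, restricted to runs whose baseline ANOVA gives p < 0.05. Rejection of a true null:

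| ρ | Unadjusted ANOVA | ANCOVA |
|---|---|---|
| 0.5 | 16.6% | 5.4% |
| 0.7 | 33.2% | 4.8% |
| 0.8 | 41.5% | 4.2% |

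If the outcome's own baseline enters only after such a test, overall type I error is 4.4%, 3.6% and 3.0%. That is conservative, not inflated.

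**6. How often the covariate rule would act.** With m independent baseline tests at 0.05, P(at least one difference) = 1 − 0.95^m. For m = 20 this is 64.2%; for m = 10 it is 40.1%. The choice of 20 is an assumption. Section 2.4 and the outcome list give more baseline variables than that once the six SFT tests are counted, but many are correlated, which lowers the figure.

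**The case against.** A reader might infer that functional outcomes are excluded from ANCOVA and left with tests that ignore their baselines. The text does not support that. The ANCOVA sentence opens with primary and secondary outcomes, so loose drafting is as plausible as a decision to exclude function. The paired tests and the change regression do use functional baselines, and the covariate rule could bring a functional baseline score into the model. What remains is that none of these is specified as a baseline-adjusted group comparison. The paired tests are within group, no group term is stated for the regression, and entry through the covariate rule depends on chance.

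It is also fair to say that the rule speaks of differences being observed, not of significance. Selection at p < 0.05 is an inference, though the baseline tests and the 0.05 threshold are the section's only stated means of finding such differences. Nor is the rule shown to inflate type I error. For cognition the pre-test score is always in the model, so only the additional covariates vary.

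Finally, ANCOVA can be read as the lead analysis for cognition, and a formal ranking may sit in an analysis plan that is not shown. That stands, so the 7.5–8.7% applies only if either test is accepted. It does not settle function, where the sentence that would name the lead analysis contradicts itself.

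**Conclusion.** The point holds as an inconsistency within the ANCOVA sentence, together with a data-dependent covariate rule and two unranked tests for cognition. It should be corrected, but it does not invalidate the design, and the sample size is not in question.

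The size is conditional. At ρ = 0.5–0.7, N = 186 and f = 0.23, adjustment raises power from 80% to 91–98% if f is on the raw post-score scale. If f is on the adjusted scale, the unadjusted test has 67–50%. The document does not say which scale applies, but precision is lost without adjustment in both cases. The 64% figure requires 20 independent tests and is an upper guide for that number.

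The regression relates change in one outcome to change in another. Both are measured after randomisation, so it describes association and cannot by itself show the effect of exercise.

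**What to change.** - State that the between-group analysis of every primary and secondary outcome analysed as a quantitative score, including the SFT items, BBS, IADL and GDS-15, is ANCOVA of the 12-week score on group and that outcome's own baseline.
- Fix the covariate set in advance. It should include sex, because the IADL range differs between women and men.
- Delete the rule that adds covariates when baseline differences are observed.
- Make the unadjusted 12-week ANOVA or Kruskal–Wallis descriptive or supportive.
- Label the change-on-change regression as exploratory association.
- If IPAQ is analysed in its low, moderate and high categories (Section 3.1.2), leave it outside this ANCOVA and name a method suited to categories.

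The cost is a few sentences in the analysis section or the analysis plan. The data are already to be collected and the named software fits the model.

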## 6. Discussion

The public health impact of Alzheimer’s disease is enormous [2,4,5]. Several studies have focused on the potential benefits of non-pharmacological approaches in patients with dementia [7]. In recent years, there is more interest in the role of physical exercise [8,9].

According to studies, it appears that systematic exercise, through a variety of mechanisms, can promote brain function and maintain and improve both cognitive functions and physical functions in elderly persons, as well as in persons with dementia [69,70,71,72].

Unfortunately, in various previous studies, there is no mention of the level of intensity, duration, and frequency of the exercise required [14,73,74,75], for an optimal exercise intervention in persons with Alzheimer’s disease. It is also possible that the benefits of exercise in the intervention groups, in terms of cognitive function, are greater in magnitude when compared to the control (no intervention) groups [73]. The use of a control group is essential to identify any differences between interventions [75]. Very few studies have supplemented data from the control group and no similar studies have been conducted in elderly adults with dementia (AD) [8].

There have been more studies in aerobic exercise and mixed interventions, while there have not been many studies regarding resistance interventions [9]. The comparison between resistance exercise on the one hand, and the combined intervention of both aerobic and resistance exercise on the other, has not been studied.

Findings regarding the cognitive benefits of exercise as a treatment for AD are inconsistent [10,11,14,71]. Inconsistencies in cognitive findings may be explained by methodological factors, such as differences in study samples and exercise parameters [10,11,14,71,73,74,75]. Moreover, another significant factor which has not been acknowledged as such, concerns inter-individual differences in exercise responses [10,11]. The methodology differences of the studies make it difficult to draw definitive conclusions about the optimal intervention in the cognitive and physical function for the optimal result, as regards the type of exercise, the duration, the frequency, and the intensity [10,11,14,71,73,74,75].

Exercise represents a viable, low-cost, personalized, and widely available, effective non-pharmacological treatment option in cognitive decline [64].

Several researchers suggest that interventions comprising home exercise programs are effective for older adults [76]. In addition, home exercise programs are cost-effective, and many older adults can benefit, since there are various limitations in accessing on-site programs in care centers [3,64,76].

## 7. Expected Results and Possible Benefits

Exercise seems to be promising for both prevention and improvement of cognitive–physical function as well as overall functioning, with evident effects on daily activities among both elderly and dementia patients.

This randomized controlled trial will contribute evidence on the potential effects of a supervised physical exercise program for persons with mild dementia (AD) living at home. Given that physical activity and exercise has a positive effect on health at any age, if the effect of exercise on persons with AD dementia is documented in our study, it could then complement medical treatment. It would also help physical therapists to design an individualized and appropriate exercise program for older persons with mild dementia in the community, in a way that can be implemented at home. In this context, regardless of results, there will be maximum objective benefit to public health.

